#### Outcome measures

The primary outcome is the number of referrals for VR per 1000 patients per month (Adoption). To assess this outcome, we will review free text annotations. Two investigators will review a random sample of free text annotations to determine which terms are used for the referrals. We will use these terms to identify referrals for VR in patients with vestibular symptoms.

Secondary outcomes are the number of prescriptions for anti-vertigo drugs, GP consultations for vestibular symptoms, and referrals to physiotherapists, ENT specialists, neurologists, and geriatricians per 1000 patients per month (Effectiveness).

#### Analysis

We will analyse the number of patients with referrals for VR, prescriptions for anti-vertigo drugs, GP consultations for vestibular symptoms, and referrals to physiotherapists and secondary care using descriptive statistics. We will use monthly measurements in the period before (April 2021–March 2023; 24 data points) and after (April 2023–March 2025; 24 data points) implementation for the interrupted time series. A segmented regression analysis will be performed to compare outcomes between these two periods. This analysis uses statistical models to estimate the level and trend in the pre-intervention segment and changes in level and trend after the intervention [35]. By doing so, we can evaluate the overall effect of the implementation. To explore the effectiveness of the individual components of our strategy, we will compare changes in levels and trends between general practices that have been exposed to that specific component and general practices that have not been exposed. Figure 2 shows an example of how we are going to assess the effectiveness of the individual components. Descriptive statistics will be performed with IBM SPSS Statistics (version 28.0) and the segmented regression analysis will be performed with R software (version 4.2.1).

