**Supplementary Information:**

The online version contains supplementary material available at 10.1186/s43058-023-00524-1.

Contributions to the literature
There is substantial literature on implementation strategies in primary care. However, it remains unclear which ones are the most effective.As one of the first studies to evaluate a nationwide implementation of an innovative treatment in Dutch primary care, we expect to provide relevant insights for future implementation projects.We will employ several research methods, including an interrupted time series, to evaluate the implementation. An interrupted time series is considered the strongest design when a randomised controlled trial is not feasible.By evaluating the effectiveness of the individual components of our implementation strategy, we can provide guidance to others in the development of strategies.

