^a^International Classification of Primary Care codes

^b^Anatomical Therapeutic Chemical codes

We will collect data on demographic characteristics, registered ICPC codes for vestibular symptoms and comorbidity, prescriptions for anti-vertigo drugs, GP consultations for vestibular symptoms, and characteristics of the general practices (e.g. degree of urbanisation). Table 2 shows an overview of the variables, including those that are used for the interrupted time series (phase 3.1).

**Table 2 Tab2:** Overview of variables for retrospective observational cohort study (phase 1) and interrupted time series (phase 3)

	**Variable**	**Definition**
**Patient characteristics**	Age	In years at time of registration ICPC code for vestibular symptoms
	Sex	Male or female
	Diagnosed vestibular disorder	According to ICPC code (see Table 1)
	Comorbidity	According to the following ICPC codes: K86 (Hypertension uncomplicated), K87 (Hypertension complicated), K83 (Heart valve disease), K84 (Heart disease other), K75 (Acute myocardial infarction), K76 (Ischaemic heart disease without angina), T90 (Diabetes), K89 (Transient cerebral ischaemia), K90 (Stroke/cerebrovascular accident), P74 (Anxiety disorder/anxiety state), P76 (Depressive disorder), A49.02 (Polypharmacy)
**General practice characteristics**	Registered patients	Total number of patients registered at practice per year and total number of adult patients (aged 18 years and over) registered at practice per year
	Employed general practitioners	Total number of general practitioners per year with patients registered to their name
	Degree of urbanisation	Based on 4-digit postal code: not/hardly urbanised (< 1.000 surrounding addresses), moderately urbanised (1.000–1.500 surrounding addresses), strongly urbanised (1.500–2.500 surrounding addresses), and extremely urbanised (> 2.500 surrounding addresses)
**Other**	Date of registration ICPC code for vestibular symptoms	-
	Date of registration and deregistration at general practice	-
	Referral for vestibular rehabilitation^a^	As described in electronic patient record
	Prescription for anti-vertigo drug	According to the ATC code (see Table 1)
	Date of prescription	-
	Referrals to physiotherapist, ENT specialist, neurologist, and/or geriatrician^a^	As described in electronic patient record
	GP consultations	Total number of GP consultations (all types of consultations, including telephone consultations and home visits) per patient per year for vestibular symptoms

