### Multicomponent implementation strategy

The strategy contains the following components:Guideline adaptationsThe Dutch College of General Practitioners’ clinical guideline for vestibular symptoms will include a recommendation for internet-based VR together with a hyperlink to Vertigo Training. In addition, a hyperlink to this intervention will be included in regional transmural agreements.Mass and target marketing strategyWe will generate national attention for chronic vestibular symptoms and the intervention using mass media (e.g. press releases, newspapers, radio and television shows, and social media). To reach healthcare providers, we will collaborate with Dutch medical journals. We will also collaborate with the patient platform Thuisarts.nl, the most popular visited medical website by patients nationwide [32]. This platform will inform patients about VR, provide instructions for the exercises, and add a hyperlink to Vertigo Training. Furthermore, the patient association will actively inform their members about the availability of the intervention. Lastly, we have developed an infographic that contains information on Vertigo Training. GPs can use this infographic in their waiting room and consulting room to maximise exposure to patients and as a reminder to the availability of the intervention. This infographic will be disseminated through media channels and along with the guideline for PTAMs.Pharmacotherapeutic audit and feedback meetingsWe will provide guidelines for PTAMs as a way to encourage GPs to stop prescribing anti-vertigo drugs and start referring patients to (internet-based) VR. In the Netherlands, these meetings are regularly organised by pharmacists and GPs in order to improve evidence based prescribing behaviour. GPs will see how they perform compared to their peers using anonymised prescription data extracted from electronic patient records. We will actively promote the PTAM guidelines to general practices connected to the academic general practice networks.Education for GPs, patients, and physiotherapistsWe will offer free education to GPs (in training), patients, and physiotherapists (in training) to improve their knowledge on chronic vestibular symptoms and VR. For instance, we will develop an e-learning module and host webinars.Clinical decision supportWe aim to add automatic recommendations for (internet-based) VR to electronic patient records. This recommendation would show up when a GP registers a vestibular ICPC code as a way to support them in choosing VR (instead of anti-vertigo drugs).Local championsWe aim to recruit GPs from different regions throughout the Netherlands to act as local champions. Their role will be to encourage colleagues to use (internet-based) VR and to organise PTAMs. Furthermore, we will motivate local champions to start their own additional implementation activities.

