The main strength of this study lies in its employed research methods. For the evaluation of the implementation, we will carry out both an interrupted time series and a prospective observational cohort study. An interrupted time series is considered the strongest design to evaluate the effect of an intervention when a RCT is not feasible [33]. By additionally employing a qualitative research method, we can enrich the evidence. Furthermore, by regularly analysing prospective data from Vertigo Training and identifying barriers and facilitators, we can tailor our implementation strategy and increase the effectiveness of our implementation. Lastly, we will use routine primary care data from more than 1.2 million patients registered at general practices throughout the Netherlands in addition to data from participants using Vertigo Training. This supports the generalisability of our results. There are also methodological limitations to this study. As the effectiveness of the individual components of our strategy will be evaluated with an interrupted time series on general practice level, we have to make several assumptions. For instance, when one GP from a general practice with multiple GPs will attend a PTAM, we assume that this GP will have an impact on all patients who are registered at that general practice. This will have an influence on the estimation of the effectiveness. In addition, it will not be feasible to determine for all components whether or not general practices are exposed. We will, for example, not be able to separate who has been exposed to the mass marketing strategy and who has not been exposed. We are therefore restricted in measuring whether exposure to a specific component resulted in a change in outcomes. Furthermore, as patients can also perform the exercises using the patient platform Thuisarts.nl, it may be possible that only a selected group (e.g. patients with advanced digital skills) will use Vertigo Training, introducing bias into our data. We will not be able to gather data from patients using Thuisarts.nl to increase the validity of our results. Another consequence of this is that we cannot tailor our strategy to the needs of this specific patient group. The same accounts for patients with vestibular symptoms that would have an indication for Vertigo Training, but were not referred to the treatment and/or did not start the treatment. Lastly, Vertigo Training has broad inclusion criteria. Therefore, some participants might benefit less from the intervention than others. For example, the Epley manoeuver is more effective in patients with benign paroxysmal positional vertigo than VR in the short term [11]. This might influence the estimation of the effect of Vertigo Training.

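### The one-component-at-a-time contrast can credit one component with the effect of another that is delivered alongside it

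*Protocol article*

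**What the plan says.** The second aim in the section on study aims and hypotheses is to learn how well the individual components work. The interrupted time series Analysis section sets out the method and marks it as exploratory ("To explore the effectiveness of the individual components of our strategy"): for a given component, the plan is to "compare changes in levels and trends between general practices that have been exposed to that specific component and general practices that have not been exposed". It does not mention exposure to the other components. It refers to Fig. 2 for an example, which is not visible here.

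The Phase 2 section on the multicomponent strategy describes how the components reach practices. Of local champions it says: "Their role will be to encourage colleagues to use (internet-based) VR and to organise PTAMs". Of the marketing infographic it says: "This infographic will be disseminated through media channels and along with the guideline for PTAMs".

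The Discussion names two limits of the component analysis. When one GP of a practice attends a PTAM, "we assume that this GP will have an impact on all patients who are registered at that general practice". Exposure also cannot be established for every component, with mass marketing given as an example. The Discussion does not say that exposures to different components may coincide. The box on contributions to the literature expects of the component results that "we can provide guidance to others in the development of strategies".

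**The concern.** A comparison of practices with and without one component isolates that component only if the two groups are otherwise similarly exposed to the rest of the strategy. Here the strategy itself works against that. A champion's job includes organising PTAMs, so practices that hold a PTAM are likely to be those that a champion also encourages directly. If that direct encouragement raises VR referrals, the PTAM contrast picks it up even if the meeting itself adds nothing.

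Comparing changes in level and trend, rather than raw rates, removes stable differences between practices. It does not remove a second component that starts in the same post-implementation period, because that component also changes the level or trend.

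At stake is the second aim. A component with little effect of its own could look effective, and others might build it into their strategies on the strength of the promised guidance.

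**Working it through.** **Inputs from the article.** 24 monthly points before and 24 after implementation (April 2021–March 2023 and April 2023–March 2025); counting the months reproduces both figures. 269 practices, stated for Phase 1; the time series uses the same collaboration. The article gives no co-exposure rates, component effect sizes or practice-level standard deviation, so the values used for these below are assumptions.

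**Formula.** Let A be the component under study (say, PTAM) and B another that overlaps with it (say, the champion's direct encouragement). If effects add up and both fall in the post-implementation period:

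- mean change in A-exposed practices = background change + effect of A + effect of B × P(B | A)
- mean change in A-unexposed practices = background change + effect of B × P(B | not A)
- difference = effect of A + effect of B × [P(B | A) − P(B | not A)]

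The last term is the bias. The background change cancels; B does not, unless co-exposure is balanced.

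**Numbers (co-exposure rates assumed).**

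| P(B given A) | P(B given not A) | Bias, as a share of B's effect |
|---|---|---|
| 0.30 | 0.30 | 0.30 − 0.30 = 0 |
| 0.50 | 0.30 | 0.50 − 0.30 = 0.20 |
| 0.70 | 0.30 | 0.70 − 0.30 = 0.40 |
| 0.80 | 0.20 | 0.80 − 0.20 = 0.60 |
| 0.90 | 0.10 | 0.90 − 0.10 = 0.80 |

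**Simulation check.** 269 practices, 30% exposed to A, true effect of A = 0, effect of B = 1, standard deviation of the practice-level change 1.5, 1000 runs, ordinary least squares, two-sided 5% level. All settings except the number of practices are assumed.

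| Co-exposure | A alone: mean estimate | A alone: rejections | A and B together: mean estimate | A and B together: rejections | Standard error of A, alone → together |
|---|---|---|---|---|---|
| 30/30 | 0.00 | 6% | 0.00 | 5% | 0.21 → 0.20 |
| 70/30 | 0.40 | 49% | 0.01 | 4% | 0.20 → 0.21 |
| 90/10 | 0.79 | 97% | −0.03 | 6% | 0.21 → 0.33 |

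The simulated means match the formula. Fitting both components together removes the bias in these settings. It costs almost no precision at moderate overlap and a clear amount at heavy overlap. The rejection rates depend on the assumed standard deviation and effect; the bias as a share of B's effect does not.

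**The case against.** **PTAMs organised by a champion are part of what the champion achieves.** This stands. A reader might infer that the champion contrast is biased because it contains the PTAM effect. The article does not support that: organising PTAMs is part of the champion's role, so PTAMs that happen because of a champion belong to the champion's total effect. The clear bias runs the other way, into the PTAM contrast. A joint model likewise gives only the part of the champion effect that does not pass through PTAMs, and must be labelled so.

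**The Discussion already discloses the limits.** In part. A reader might infer that counting a practice as exposed when one GP attended is an overlooked dilution. The Discussion states this assumption and says that it influences the estimate. With full spillover inside the practice, as assumed there, nothing is diluted, and scaling by the share of GPs would merely substitute an assumption of no spillover. The Discussion also concedes that mass-marketing exposure cannot be separated, which covers much of the infographic overlap. It does not mention coinciding exposures.

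**The detail may lie elsewhere.** A reader might infer that months before a practice's own PTAM are counted as exposed. The text fixes no break date for the component comparison and refers to a figure not visible here; staggered uptake would also appear partly as a change in trend, which the plan estimates. That inference is not supported. A fuller analysis plan may add adjustment, but the contrast as printed is defined by one component only.

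**The analysis is exploratory and the magnitudes are hypothetical.** Both are true. With balanced co-exposure there is no bias. But the exploratory label sits uneasily with the promise of guidance to others.

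**Conclusion.** The point holds in a limited form. As printed, the component contrast ignores exposure to other components, the strategy makes some exposures go together, and the limitations do not say so. One component can therefore be credited with part of another's effect; the clearest case is the PTAM contrast absorbing the champion's direct encouragement. The size is the other component's effect times the co-exposure difference: 0 if balanced, 40% at an assumed 70/30, 60% at an assumed 80/20. This rests on additive effects and on co-exposure rates that the article does not give.

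It would go too far to conclude that effects will be misattributed, or that this applies to every component, since some components have no measurable exposure and are outside the comparison. The overall before-after analysis, including that of the primary outcome, is unaffected. The matter deserves correction because it bears on the study's second aim and the remedy is cheap.

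**What to change.** - Fit one practice-month segmented model with all recordable component exposures together, each starting in the practice's own first exposure month.
- Report how far the exposures overlap, for example by cross-tabulating them by practice, so that readers can see which components can be told apart.
- State that the champion coefficient in this model excludes effects that pass through PTAMs, and give the unadjusted champion contrast beside it as the total association.
- Limit component conclusions to recordable components and describe them as associations, since practices were not allocated to components at random. Add coinciding exposures to the limitations and bring the guidance statement into line.
- Optionally, as a sensitivity analysis only, scale PTAM exposure by the share of GPs who attended. Table 2 already collects the denominator ("Total number of general practitioners per year with patients registered to their name"); attendance counts would have to be added.

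The cost is some analysis work and recording the month of first exposure per practice and component. No new patient data are needed. Intervals will widen where exposures nearly coincide; in the illustration the standard error rose from 0.20 to 0.21 at 70/30 and from 0.21 to 0.33 at 90/10.

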**Fig. 2 Fig2:**
[figure not shown]
Example of measuring the effectiveness of the individual components. *GPs* = general practitioners, *PTAM* = pharmacotherapeutic audit and feedback meeting

### Prospective observational cohort study

#### Study design and data collection

We reported this prospective observational cohort study in line with the The Strengthening the Reporting of Observational Studies in Epidemiology (STROBE) Statement (Additional file 4) [25]. During the implementation period (April 2023–March 2025), we will gather data from participants who use Vertigo Training and who give informed consent for the collection and analysis of their data. Participants who do not give informed consent can still use the application. We will evaluate the usage of Vertigo Training and the characteristics of participants. The evaluation will take place on a regular basis and we will adapt our implementation strategy accordingly. We will also determine whether certain characteristics are associated with successful treatment.

Data on the usage of Vertigo Training will be collected. We will also gather data on demographic characteristics, diagnosis and treatment of vestibular symptoms, and severity of vestibular symptoms according to the vertigo symptom scale-short form (VSS-SF) [36], using an online voluntary questionnaire at baseline. The VSS-SF will additionally be evaluated at 6 weeks, 3 months and 6 months. Table 4 shows an overview of variables.

**Table 4 Tab4:** Overview of variables for prospective observational cohort study

Variable	Definition
Age	In years at time of start intervention
Gender	Male, female, other
Place of residence	-
Diagnosed vestibular disorder	Anamnestic
Education level	Primary education, prevocational secondary education, senior general secondary education, pre-university education, senior secondary vocational education, higher vocational education and university education
Migration background	Yes (if at least one parent was born abroad) or no
Received medical care for vestibular symptoms	Yes (from general practitioner, medical doctor at hospital, medical doctor at other type of clinic, physiotherapist, and/or other healthcare provider) or no
Prescription for anti-vertigo drug in past	Yes or no
Vestibular symptoms	According to vertigo symptom scale-short form at baseline, 6 weeks, 3 months, and 6 months
Acquaintance with Vertigo Training	Through the patient association, the internet, a healthcare provider, friends, social media, and/or other ways

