## Background

Vestibular symptoms, such as dizziness and vertigo, affect approximately 25% of the general population at some point in their lives [1]. These complaints are therefore frequently seen in general practice. In a significant number of patients with vestibular hypofunction, vestibular symptoms become persistent and they develop a chronic vestibular syndrome [2]. For instance, 30–40% of patients with vestibular neuritis still experience dizziness after 6 months [3]. One of the reasons includes failure of the vestibular compensation process, which involves adaptation of the nervous system to vestibular damage [4]. According to the International Classification of Vestibular Disorders, a chronic vestibular syndrome comprises chronic vestibular symptoms lasting months to years and includes features suggestive of persistent vestibular system dysfunction [5, 6]. The prevalence of chronic vestibular symptoms in the adult population ranges between 1.4 and 4.8% [7, 8].

Adequate treatment of patients with vestibular symptoms, and especially chronic vestibular symptoms, is of utmost importance because the consequences are far-reaching. Many patients experience a reduced quality of life. Older patients, for instance, may experience loneliness, isolation, and decreased self-esteem [3, 9]. Furthermore, vestibular symptoms are associated with a high financial burden as a result of increased healthcare utilisation, increased frequency of falls, and sick leave [8, 10].

Vestibular rehabilitation (VR) is an exercise-based treatment that stimulates vestibular compensation. It is proven to be a safe and effective treatment for both patients with unilateral vestibular hypofunction (e.g. vestibular neuritis), and bilateral vestibular hypofunction (e.g. vestibulopathy due to aminoglycoside ototoxicity) [11, 12]. In addition, a systematic review in 2018 showed that VR is effective in reducing symptoms in patients with chronic vestibular symptoms, regardless of the original cause [13]. Despite strong scientific evidence, VR is underused in general practice, mostly due to a lack of knowledge [14, 15]. In contrast, off-label anti-vertigo drugs are prescribed regularly, despite low quality of evidence [16–18].

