## Phase 2: nationwide implementation of Vertigo training

We will embed Vertigo Training in Dutch primary care from April 2023 onwards. The online application will be made freely available through the website www.gezondheidsmeter.nl. More information on Vertigo Training is described in Table 3.

**Table 3 Tab3:** Information on intervention to be implemented: Vertigo Training

Vertigo Training is a freely accessible internet-based intervention that contains six exercises. These six exercises include eye, head, and body movements that aim to stimulate vestibular compensation, a process in which the nervous system reorganises and is able to overcome damage of the vestibular system. In addition, a form of exposure-based behavioural therapy takes place by deliberately provoking vestibular symptoms in a controlled environment. The application prescribes a personal exercise regimen based on the severity of symptoms while performing the exercises. Patients are asked to perform the exercises twice a day for 10 min. The regimen lasts 6 weeks. Patients can start with Vertigo Training on their own initiative, or they can be referred to the treatment by a healthcare provider. They can perform the exercises by themselves, but it is also possible to receive support from a healthcare provider, such as a physiotherapist. In the Netherlands, patients can access physiotherapy through self-referrals.
Patients are eligible for Vertigo Training if they are 18 years and older, if they have had vestibular symptoms for at least one month during most days of the week, and if these symptoms are provoked or exacerbated by head movements or visual stimuli.

We created an implementation plan, involved local implementation specialists, and identified relevant stakeholders (i.e. GPs, ENT specialists, physiotherapists, and patients with vestibular symptoms) to adapt our implementation strategy to their needs. The final strategy consists of the following components: guideline adaptations; mass and target marketing strategy; pharmacotherapeutic audit and feedback meetings (PTAMs); education for GPs, patients, and physiotherapists; clinical decision support; and local champions. We will elaborate on these components further on.

We used the Standards for Reporting Implementation Studies (StaRI) Statement to report the implementation strategy and the intervention (Additional file 3) [31].

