#### Outcome measures

Outcomes are the number of participants using Vertigo Training (Reach), the number of participants finishing the exercise regimen (Implementation), and the descriptive characteristics of these participants (Reach). We will also evaluate characteristics associated with successful treatment (Effectiveness). Successful treatment will be defined as a change of 3 points or more in the VSS-SF score between baseline and 3 months, which indicates a clinically relevant difference in vestibular symptoms.

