#### Analysis

Descriptive statistics will be used to assess the usage and characteristics of participants. In addition, we will perform a mixed-effects logistic regression analysis to evaluate whether these characteristics are associated with successful treatment. We will use IBM SPSS Statistics (version 28.0) for the descriptive statistics and the mixed-effects logistic regression analysis will be performed with R software (version 4.2.1).

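### The Vertigo Training cohort takes users from one month of symptoms but lists no symptom duration, so associations with 3-month success can be confounded by natural recovery

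*Protocol article*

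**What the plan says.** **Who enters.** Table 3 (Phase 2) makes adults eligible "if they have had vestibular symptoms for at least one month during most days of the week", provided head movements or visual stimuli provoke or worsen the symptoms. It sets no upper limit on duration. The prospective cohort in Phase 3 adds no stricter rule: "we will gather data from participants who use Vertigo Training and who give informed consent for the collection and analysis of their data".

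**What is recorded.** Under Study design and data collection, the baseline questionnaire is described thus: "We will also gather data on demographic characteristics, diagnosis and treatment of vestibular symptoms, and severity of vestibular symptoms". The text then says "Table 4 shows an overview of variables". The ten rows of that table are age, gender, place of residence, diagnosed disorder, education, migration background, medical care received, past anti-vertigo prescription, VSS-SF, and how the participant came to know the application.

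**Outcome and model.** "Successful treatment will be defined as a change of 3 points or more in the VSS-SF score between baseline and 3 months". Characteristics associated with success are filed under the Effectiveness dimension of RE-AIM. The Analysis section adds: "we will perform a mixed-effects logistic regression analysis to evaluate whether these characteristics are associated with successful treatment".

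**Natural course.** The Background gives one figure: "30–40% of patients with vestibular neuritis still experience dizziness after 6 months". It also notes that "a chronic vestibular syndrome comprises chronic vestibular symptoms lasting months to years", and the study aim concerns patients with chronic symptoms.

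**The concern.** Duration is part of the eligibility rule and a plausible strong predictor of how much spontaneous recovery is still to come. Someone who enters one month after onset is followed to about month four, when recovery may still be under way. Someone with years of symptoms is much less likely to recover unaided in those 3 months. Without duration, the model cannot tell these participants apart directly.

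Several listed characteristics plausibly go with longer illness. There has been more time to see a doctor, receive a prescription, obtain a diagnosis, or hear of the application through the patient association. If they do, their coefficients can carry part of the duration effect and be read as showing who benefits from the application.

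The study also could not say how many users belong to the chronic group named in its aim. The Discussion concedes that broad inclusion criteria mean differing benefit, but it mentions neither duration nor natural recovery.

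**Working it through.** The protocol gives no sample size, success rate or expected association for this cohort, so there is no figure of its own to reproduce. The factual part is settled by reading: entry is from one month, there is no upper limit, and neither the text nor Table 4 has an onset or duration variable. The arithmetic below is illustrative only.

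**Set-up.** Take two strata, short and long duration, and a yes/no characteristic with no effect on success within either stratum. If a share *f* of a group is short-duration, its success rate is p = f·p_short + (1 − f)·p_long. The crude odds ratio is [p₁/(1 − p₁)] / [p₀/(1 − p₀)]. Within strata the true odds ratio is 1.00.

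**Illustration A: untreated recovery taken as success.**
- From the Background, for vestibular neuritis only: 30% to 40% still dizzy at 6 months, so by subtraction 60% to 70% are not.
- Assuming a constant hazard, h = −ln(S₆)/6 = 0.201 per month (S₆ = 0.30) or 0.153 per month (S₆ = 0.40).
- Recovery in any 3 months is 1 − exp(−3h) = 45% or 37%.
- Assume 10% success in long-standing patients. The odds ratio for duration itself is then 7.4 or 5.2.
- Assume 50% short-duration in one group and 20% in the other. With S₆ = 0.30, success is 27.6% v 17.0%, a crude odds ratio of 1.86. With S₆ = 0.40, it is 23.4% v 15.4%, a crude odds ratio of 1.68.

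**Illustration B: milder contrast, since everyone uses the application.** Assume 40% success in long duration and 50%, 60% or 70% in short duration. Keep the mix at 50% v 20%.

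| Success, short duration | Group success (50% v 20% short) | Crude odds ratio |
|---|---|---|
| 50% | 45% v 42% | 1.13 |
| 60% | 50% v 44% | 1.27 |
| 70% | 55% v 46% | 1.43 |

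**Illustration C: the success rates of B with other mixes, characteristic more common in long duration.**
- Shares of short duration 20% v 30% and 50% success in short duration: 42.0% v 43.0%, odds ratio 0.96.
- Shares 10% v 50% and 70% success in short duration: 43.0% v 55.0%, odds ratio 0.62 (inverse 1/0.62 = 1.6).
- Equal shares (20% v 20%): odds ratio 1.00 whatever the success rates.

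With an assumed 500 per group, the chance of a significant result in the direction of the bias is 5% in the first of these cases and 97% in the second.

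**Reading.** Over these inputs the crude odds ratio for a null characteristic lies between 1.0 and about 1.9, or the inverse. It departs from 1 only if duration differs between the groups compared.

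**The case against.** A reader might go further and infer that the associations *will* be confounded and mainly show who was recovering anyway. The protocol does not support that. Bias requires duration to differ across the characteristic studied, and nothing in the protocol shows that it does.

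The larger figures are also fragile. The 30% to 40% describes persisting dizziness in vestibular neuritis, whereas the cohort covers all causes and success is a 3-point VSS-SF change in people using the application. The 10% for long-standing patients has no source. The Background reports clinically relevant improvement in chronic patients who used the application in the earlier randomised trial, which points to a higher rate. With 40% instead, and 50% to 70% in short duration, the odds ratio falls to about 1.1 to 1.4. These objections stand.

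Other objections stand in part:
- Diagnosis, care received, past prescription and baseline VSS-SF would absorb some of the duration effect if modelled together. The figures above are crude, and what remains after adjustment is unknown.
- The stated question is one of association, so an omitted predictor limits interpretation and does not falsify the result. Filing the result under Effectiveness nevertheless invites the stronger reading.
- The questionnaire is not shown and the application may screen for the one-month rule. A threshold check would not yield a usable duration variable, however, and Table 4 is detailed enough to list seven education levels.
- A reader might infer that the omission is beyond repair once data are collected. Participants are contacted again at 6 weeks, 3 months and 6 months, so onset could still be asked, with more recall error.
- Recording duration does not remove natural recovery within a duration band. It reduces only the difference in recovery between the groups compared.

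**Conclusion.** The point holds in limited form. The cohort takes users from one month of symptoms without upper limit, and the listed variables omit onset and duration. Associations with an uncontrolled 3-month change can therefore be confounded by differing natural recovery, for any characteristic related to duration. Diagnosis and baseline VSS-SF replace duration only partly.

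The size cannot be derived from the protocol. The range of about 1.0 to 1.9 (or the inverse) for a null characteristic rests on assumed success rates, assumed shares of short duration and, at the upper end, a constant hazard applied to a neuritis figure. It shows that the bias could range from nothing to something that would be reported as a finding; it is not an estimate.

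The matter concerns the prospective cohort and leaves the interrupted time series untouched. It is worth correcting because the change is cheap and also lets the study identify the chronic group that its aim names.

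**What to change.** - Add one item to the baseline questionnaire and to Table 4: time since onset, for example 1–3, 3–6, 6–12 and more than 12 months.
- Include it, together with baseline VSS-SF, as fixed covariates in the mixed-effects logistic model.
- Report the success proportion by duration band, and base statements about chronic symptoms on the longer bands.
- State in the report that, without an untreated comparator, improvement within a band still includes natural recovery.
- For participants already enrolled, ask about onset at a follow-up questionnaire and note the greater recall error.

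The cost is one more question in an online form that already covers ten variables, one more covariate in the model, and recall error in the reported onset.
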